**Replication:**

Replication is essential in single-case experimental designs to strengthen internal and external validity by confirming causality and generalisability of the results. It helps reduce uncertainty, especially when different visual criteria or statistical methods yield conflicting conclusions [61]. This study uses both direct and systematic replication. **Direct replication** tests the reliability of effects within a similar population (i.e., inter-subject replication) [62]. In our study, this involves conducting another multiple-baseline experiment with at least three tiers within the same participant group. This is particularly important for ED patients with mild-to-moderate injuries (*Sample* 1, ISS < 15), who serve as the reference population, ensuring consistency across individuals with comparable presentations. **Systematic replication**, by contrast, typically involves modifying aspects of the original study, such as the setting, behaviour, participants, and components of the intervention [63]. In this study, replicability will be examined by applying the intervention to three additional groups within the emergency care setting:*Sample* 2: More severely injured participants (ISS ≥ 15).*Sample* 3: Non-injured patients with acute stress from medical events.*Sample* 4: Health workers from the ED exposed to workplace stress.

By varying participant characteristics and stressors, systematic replication helps determine whether the intervention’s effects extend beyond the initial sample, enhancing its relevance across diverse real-world emergency care contexts. This dual approach strengthens both the reliability and broader applicability of the intervention.

#### 2.2.2. Co-Design Component

The nested, Co-design component, whereby participant perspectives have the capacity to alter and shape the larger-scale trial, aims to evaluate the feasibility of the intervention. *Participants’ adherence, preliminary engagement,* and *satisfaction* with the WeCare program and wearables used will be examined, including the user *acceptability* and *usability* based on individual experience (Figure 1). Mixed methods will be used for this component, including quantitative approaches that provide objective feasibility and acceptability data, complemented by qualitative interviews/focus groups. Participants from each sample group will be invited to provide rich, detailed insights into their experiences (see Section 2.6.3 for details). The findings will inform the co-design of a user-centred solution tailored to the needs of these populations and guide the development of a larger-scale trial for future implementation and scalability.

#### 2.2.3. Cost Analysis Component

The Cost analysis component aims to evaluate the *preliminary cost benefits* of implementing the WeCare program by quantitatively assessing changes in healthcare use and time off work (Figure 1). In this preliminary study, this data will be obtained through self-report measures, including participant diaries on frequency of healthcare visits, medication use, and number of sick leave days taken. While self-reporting provides an accessible and low-burden approach for early-stage evaluation, it will also inform the feasibility of incorporating objective cost and utilisation data (e.g., administrative records) in future larger-scale trials. It will examine whether the initial investment results in cost savings, helping to determine if the program is a viable, low-cost, and sustainable solution for improving mental wellbeing and resilience in emergency care settings.

### 2.3. Eligibility Criteria

Each sample of participants will be participating in all three components of the trial. The inclusion and exclusion criteria for each of the four samples are detailed in Table 2.

### 2.4. Recruitment, Enrolment, and Randomisation

Patients (*Samples* 1–3) presenting to the RNSH ED will be consecutively screened for study eligibility by ED personnel based on information available on the electronic medical record system. Individuals who are deemed eligible will be informed about the study and invited to participate either during their ED visit or by follow-up call or email. The ED personnel will be provided with an ethically acceptable script to use when approaching participants. If individuals express interest in the study, the ED personnel will ask permission to share their contact information with the research team. A member of the research team will contact them for further screening, and potential participants will also have the opportunity to ask questions about the study. ED healthcare workers (*Sample 4*) will be recruited through flyers displayed on ED noticeboards and wards, email invitations, or direct clinical contact with support from the ED Wellness Group at RNSH. All interested ED healthcare worker participants will be screened by the research team against the eligibility criteria before enrolling them in the study.

All participants who meet the study inclusion criteria will be provided with comprehensive study information, both verbally and through a written study advertisement and participant information sheet. Potential participants can take their time to think and decide, and if they agree to enrol in the study, they will be asked to sign a written informed consent form via a secure online REDCap platform, hosted by The University of Sydney. Potential participants will also be asked their preferred day and time to attend the introductory study session at the start of the baseline phase, where they will receive their smart watch and orientation to the study.

Once a cohort of at least 3 eligible participants is recruited, they will be enrolled concurrently, assigned a unique study number, and booked in for the introductory session. Participants will be randomly allocated to a baseline phase duration of 1, 2, or 3 weeks (i.e., 7, 11, or 15 days, respectively) depending on their tier, in accordance with the study’s single-case design standards. An independent researcher, not involved in participant recruitment, will generate a randomisation sequence using standard computerised methods to minimise bias. Randomisation will take place after the pre-baseline data is collected (Week 0) to reduce the risk of allocation bias. Investigator blinding is not feasible due to study procedures, and this is not a randomised clinical trial.

All participants who choose to enrol in the study will be automatically included in all three components of this proof-of-concept study. Upon completion of the *WeCare* program as the experimental component, research investigators will invite participants to take part in in-depth interviews. Additionally, cost data will be collected weekly throughout the duration of the study.

### 2.5. Intervention: WeCare Program

WeCare is an innovative, evidence-based, wearable-integrated wellbeing initiative designed for individuals exposed to significant stress. It delivers a 6-week, self-directed and self-reflective intervention program aimed at improving stress regulation, enhancing resilience, promoting sustainable recovery, and optimising performance and wellbeing. The program integrates biometric wearable monitoring with psychoeducation and personalised behavioural guidance to mitigate the risk of disability associated with acute (e.g., injury, trauma, or illness), chronic, or occupational stress (e.g., ED workers).

Co-designed by a multidisciplinary team of experts in mental health, injury recovery, and rehabilitation, together with individuals with lived experience, WeCare empowers participants to take charge of their health by combining real-time physiological data from wearables and behavioural science through personalised, data-informed feedback, and expert guidance.

#### 2.5.1. Wearable Integration and Personalised Data-Driven Feedback

The program employs an advance *smart ring* device (OuraRing4, Oura Health, Oulu, Finland, https://ouraring.com/terms-of-use, https://ouraring.com; accessed on 15 October 2025) to provide continuous physiological feedback to participants. Using infrared LEDs, temperature sensors, an accelerometer, and a gyroscope, the ring collects real-time biometric data, including key indicators such as HRV, respiratory rate, sleep metrics, and body temperature.

The associated app applies proprietary algorithms, which incorporate elements of machine learning/artificial intelligence to analyse the data. The app summarises daily and weekly trends, generating health summary scores related to stress, recovery, and activity. Participants will receive daily personalised, data-driven insights based on their individual physiological patterns. These insights, paired with guided reflections and practical suggestions, will support participants’ understanding of their stress and recovery cycles, as well as how their habits influence their health trajectory, encouraging self-awareness and adaptive behaviour.

#### 2.5.2. Program Framework: The “Learn–Track–Act” Paradigm

The WeCare program uses a structured “Learn–Track–Act” paradigm (Figure 3), guiding participants through a stepped, personalised process of self-awareness and behaviour change. This framework is embedded across the 6-week intervention and involves the following aspects:*Learn:* Participants engage with digital psychoeducational content on stress, wellbeing, and self-regulation strategies via factsheets, videos, and real-life stories.*Track:* Participants monitor their daily physiological data, observe trends over time, and see how their activities influence key biometrics and how they feel, using the wearable-based app.*Act:* Participants receive personalised feedback via the app and expert guidance based on their data and engage in evidence-based self-regulation practices (e.g., lifestyle adjustments, paced breathing, and mindfulness) to support stress management and recovery.

#### 2.5.3. Program Structure

Participants will be guided through the following steps (Figure 3):(1)*Making sense of stress and wellbeing* (Week 1)

Participants attend a 60–90 min psychoeducation session, delivered in person at the RNSH laboratory, or via telehealth as a pre-recorded video. This session introduces the multidimensional nature of stress and wellbeing, including its physiological manifestations. Participants are introduced to the smart ring, instructed on installation of the app, and begin continuous data and daily activity tracking. The goal of this session is to build foundational awareness and context-specific understanding of stress and wellbeing.

(2)*Knowledge is power: digging into the data* (Weeks 2–3)

Participants explore their personal biometric data to improve body awareness and recognise stress and recovery patterns. This phase encourages reflection through guided prompts and educational content, helping participants identify how stress manifests in their physiology and daily routine. The aim is to foster insight and engagement with one’s own health data as a tool for learning and growth, supporting meaningful changes. A 2-week period is required by the smart ring system to calibrate personalised recommendations for each participant.

(3)*In the driver’s seat: taking charge of my health* (Weeks 4–6, and beyond)

This final phase encourages behavioural change through experiential learning. Participants learn about healthy habits and are encouraged to self-reflect and experiment with a range of self-regulation strategies to manage stress and enhance wellbeing, such as the app’s in-built breathwork and mindfulness modules, and integrate these practices into their daily routines. Following Week 6, participants will have the option to continue the intervention for an additional two weeks using a smartwatch instead of the smart ring. Guidance will also be provided on how to design and run a personalised self-experiment beyond the core 6-week program, encouraging sustained engagement and long-term habit formation.

#### 2.5.4. Weekly Insights and Daily Practice Guidance

In addition to daily personalised data-driven feedback via the wearable app, participants will receive structured guidance through a companion digital health platform (accessible via mobile app or desktop) over the 6-week program. This guidance is delivered through a combination of weekly and daily notifications aligned with the program’s core themes to support wellbeing, self-reflection, and sustained behaviour change.

*Weekly thematic insights*: Each week, participants are provided with evidence-based content aligned with the program’s focus. This includes short readings, video resources, e-learning links, and lived-experience stories. Weekly modules also offer practical guidance to support daily wellbeing practices and activities such as journaling, breathwork, mindfulness, and lifestyle modifications.*Daily reflection prompts:* To encourage engagement and deepen learning, participants receive structured prompts that support reflection on personal experiences, habits, and progress. These prompts aim to foster self-awareness and active participation in the program and behaviour change.

Details of weekly themes, suggested activities, and reflection prompts are presented in Figure 3.

#### 2.5.5. Human and AI-Based Support

Participants will receive a brief (10–15 min) weekly check-in with a qualified member of the research team, delivered via phone or telehealth. These check-ins are designed to monitor progress, address questions, and provide personalised support. Participants may choose to share their biometric data from the smart ring device in advance to help guide these conversations and tailor feedback.

In addition to human support, the wearable app features a built-in, AI-powered smart advisor that offers 24/7 real-time guidance. This advisor provides personalised suggestions based on the participant’s ongoing biometric data and app interactions.

This blended model, combining human with AI-driven support, has been shown to enhance engagement and improve outcomes compared to digital-only interventions [49,64].

### 2.6. Outcome Measures and Data Collection

Outcomes include measures that assess the four study objectives: *Feasibility (practicality of methods), Clinical effectiveness, User acceptability*, and *Cost benefits*.

#### 2.6.1. Feasibility Outcomes

Feasibility outcomes include assessment of recruitment and data collection processes, intervention safety, participant adherence and engagement, and fidelity of program delivery and use. *Recruitment feasibility* and the *suitability of data collection methods* will be evaluated through screening logs, enrolment and retention rates, reasons for non-participation or dropout, and the proportion of missing data. A retention rate of ≥80% will be considered feasible, following traffic light criteria (green: ≥80%, amber: ≥60%, red: ≤40%) [65]. The *safety* of the intervention will be monitored via weekly self-reported adverse events. Participants will be closely monitored for any physical, psychological, or device-related issues, which will be documented and reported according to institutional protocols, contributing to the limited evidence base on the safety of digital and wearable-based interventions. *Adherence and engagement* will be assessed through smart ring wear time and usage analytics from the digital health platform, respectively, as well as users’ feedback, which will also inform evaluation of program fidelity and adherence to intervention components.

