## 2. Materials and Methods

### 2.1. Participants and Setting

Four groups of participants, including patients and ED healthcare workers in emergency care settings, will be recruited from the ED of Royal North Shore Hospital, a Level 1 Trauma Centre, in Sydney, Australia. Between 3 and 8 eligible participants will be recruited per group (at least 3 participants per experiment) for a total of up to 32 participants. The groups are as follows:*Sample* 1: Patients presenting to the ED with mild-to-moderate injuries (Injury Severity Score, ISS < 15).*Sample* 2: Patients presenting to the ED with severe injuries (ISS ≥ 15).*Sample* 3: Patients presenting to the ED with acute non-traumatic, minor-to-moderate medical complaints (Australasian Triage Scale, ATS category 3–5 = less urgent).*Sample* 4: Emergency healthcare workers exposed to workplace stress.

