### 2.7. Sample Size

Up to 32 participants will be recruited for this pilot study, up to 8 participants in each study group. Power calculation is not relevant as this is an N-of-1 pilot study using a design that has not been utilised previously.

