### 2.8. Data Analysis and Reporting

For the primary measures, graphical representation and calculation of a mean and trend line will be used to analyse changes over time and between periods. Trend analyses will also be conducted to account for unstable baselines (e.g., increasing or decreasing severity over time), providing a more nuanced understanding of change. Level- and slope-change analyses will be used to further analyse change between periods. Secondary analyses will be performed on secondary outcomes. No interim analyses will be performed in this study. The level of significance to be used will be set at *p* < 0.05 unless otherwise required. The quality of the dataset will be inspected regularly by outcome assessors for missing data. Additionally, missing or spurious data will also be inspected by one of the senior researchers. Moreover, linear mixed-effects modelling [79], a multiple regression technique that is flexible and suitable for single-case design studies, will be used to provide standardised effect sizes and measures of statistical significance. Analyses will also include evaluation of overlap between phases; for example, Tau-U will be applied as a non-parametric effect size method appropriate for single-case experimental designs.

A feasibility analysis will be also conducted using prespecified progression criteria to help guide the interpretation of pilot trial findings to decide whether, and how, a definitive RCT is feasible and should be conducted. Once all the text information from interviews is collated, qualitative data analysis will be conducted, which involves thematic analysis and directed content analysis to determine the most important themes that emerged from the participant discussions regarding the acceptability of the intervention. A summary of the results will be sent to the participants for checking, verification, and confirmation of the researcher’s interpretation of key issues and thematic understanding. The software package NVIVO will be used to analyse the qualitative data.

To ensure clarity and transparency in reporting, study findings reporting will adhere to the Single-Case Reporting guideline In BEhavioural interventions [80] and Consort Extension for reporting N-of-1 trial guidelines [81], while the qualitative component will be reported following the Consolidated Criteria for Reporting Qualitative Research (COREQ), a 32-item checklist for interviews and focus groups [82].

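### The retention traffic light assigns no colour to retention above 40% and below 60%, so whether such a result means amend or stop is not fixed in advance

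*Protocol article*

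**What the plan says.** Section 2.6.1 (Feasibility Outcomes) states that "A retention rate of ≥80% will be considered feasible", and then sets out the grading: "following traffic light criteria (green: ≥80%, amber: ≥60%, red: ≤40" per cent. Read in the natural way, green is 80% or more, amber is 60% to below 80%, and red is 40% or less.

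Section 2.8 (Data Analysis and Reporting) explains what such criteria are for. The feasibility analysis proceeds by "using prespecified progression criteria to help guide the interpretation of pilot trial findings to decide whether, and how, a definitive RCT is feasible".

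The sample size sets the possible counts. Section 2.1 says "Between 3 and 8 eligible participants will be recruited per group", and section 2.7 says "Up to 32 participants will be recruited for this pilot study, up to 8 participants in each study group". The article gives no expected retention rate.

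**The concern.** A progression criterion is useful because its meaning is fixed before the result is known. Here the lower edge of amber (60%) and the upper edge of red (40%) do not meet. A result between them satisfies none of the three inequalities, and nothing else in the article assigns that range.

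At stake is the difference between two decisions. If the uncoloured range is treated as amber, the team modifies the study and carries on towards a definitive trial. If it is treated as red, it does not. A team that finds about half its participants retained would have to choose the reading with the result in front of it, and over that range the criterion would not be prespecified in the sense of section 2.8.

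**Working it through.** There is no figure in the article to reproduce here, so the check applies the printed bands to every possible count of retained participants.

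**Inputs.** Bands from section 2.6.1: green ≥80%, amber ≥60% (so 60% to below 80%), red ≤40%. Sample size from sections 2.1 and 2.7: at least 3 per group, so 4 × 3 = 12, and at most 8 per group, so 4 × 8 = 32. An intermediate 4 × 6 = 24 is added for illustration.

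**Step 1: which counts have no colour.** A count k out of n has no colour when 0.4n < k < 0.6n.

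- n = 32: 12.8 < k < 19.2, so k = 13 to 19 (40.6% to 59.4%)
- n = 24: 9.6 < k < 14.4, so k = 10 to 14
- n = 12: 4.8 < k < 7.2, so k = 5 to 7
- n = 8 (one full group): 3.2 < k < 4.8, so k = 4
- n = 3 (one minimum group): 1.2 < k < 1.8, so no count is affected

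The full classification at n = 32 is red 0–12, no colour 13–19, amber 20–25, green 26–32. Seven of the 33 possible counts have no colour. Retention of exactly 40% or exactly 60% is classified.

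**Step 2: how likely the gap is.** Assume that participants are retained independently with a common true probability p. The chance of no colour is then the sum of C(n,k) p^k (1−p)^(n−k) over the uncoloured counts. Since the article gives no expected retention, a range of p is shown.

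| Assumed true retention | No colour, n = 32 | Red, n = 32 | No colour, n = 12 |
|---|---|---|---|
| 40% | 0.530 | 0.462 | 0.505 |
| 50% | 0.785 | 0.108 | 0.612 |
| 55% | 0.714 | 0.035 | 0.584 |
| 60% | 0.530 | 0.008 | 0.505 |
| 70% | 0.132 | 0.000 | 0.267 |
| 80% | 0.006 | 0.000 | 0.072 |

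**Step 3: whether the way of closing the gap matters.** There are two complete repairs at n = 32:

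- Red below 60%: red 0–19, amber 20–25, green 26–32.
- Amber extended to above 40%: red 0–12, amber 13–25, green 26–32.

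Under either, each of the 33 counts gets exactly one colour. The seven counts from 13 to 19 are red under the first and amber under the second, so the choice changes the decision.

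**The case against.** The best case on the other side is that little depends on this. Section 2.8 uses the criteria to help guide interpretation, which is advisory. Section 2.6.1 also looks at enrolment, reasons for dropout and missing data, so retention would not decide alone. Section 2.6.3 already foresees exploring adaptations if attrition is higher than expected. The gap is also remote if retention is near the 80% target. The limitations section concedes that digital interventions often lose more participants, but it gives no rate near 50% and describes reminders and check-ins as countermeasures.

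Most of this stands, and it limits the severity. It does not close the gap. Foreseeing adaptations does not say at what retention adaptation stops being enough, which is the job of the boundary between amber and red.

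Four stronger readings are tempting, and the article does not support them:

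- A reader might infer that the rule cannot deliver a stop. It can: 40% or less is red.
- A reader might infer that the uncoloured range has no verdict at all. It is already excluded from feasible by the 80% sentence; only amend versus stop is open.
- A reader might infer that the plan's sole numeric progression rule has failed. No other feasibility measure in this article carries a threshold, but the article condenses a fuller protocol that is not shown, and section 2.8 speaks of criteria in the plural. The point does not need this argument.
- A reader might infer that red was meant to be below 60%. The source cited for the bands is not available here, so a misprint can be neither confirmed nor excluded.

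**Conclusion.** The point holds in a limited form. The bands as printed are not exhaustive, and this follows from the three inequalities alone, without any assumption. The undefined matter is whether retention above 40% and below 60% means amend or stop.

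Its practical weight depends on the true retention rate. At n = 32 the gap is the most likely outcome if about half the participants stay, and it is negligible at the target rate. The probabilities assume independent dropout at a common rate and bands applied to all enrolled participants together; the choice of rates is illustrative.

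Severity is moderate. No effect estimate, randomisation step or safety procedure is affected. The problem is still worth correcting, because the article states the rule with all its cut-points and the rule cannot be followed as written over part of its range.

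**What to change.** Before any retention data are seen, restate the bands in section 2.6.1 so that they meet and cover 0% to 100%. Two versions do this:

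- **Stricter:** green 80% or more, amber 60% to below 80%, red below 60%.
- **More lenient:** green 80% or more, amber above 40% to below 80%, red 40% or less.

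Nothing in the article favours one over the other, so the investigators should choose, record the choice with the date, and give the reason in a sentence. The cost is one line of protocol text with no change to conduct. Under the stricter version, a result in the present gap would receive the less favourable colour.
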